### Methods in analysis to handle protocol non-adherence and any statistical methods to handle missing data {20c}

Intention-to-treat analysis will be executed. All participants that are randomized, including treatment dropouts and study dropouts will be included in the main analysis. Maximum likelihood estimation will be used for missing data. In order to determine the robustness of the results, two sensitivity analyses will be conducted: one with the data of all participants that completed all assessments and the intervention, and one with the data of all participants that completed all the assessments but not the intervention (treatment dropouts). Participants will be considered a treatment dropout when they did not complete the game. When a parent has not (fully) read the complementary information brochure, this is not considered as a treatment dropout. The latter also accounts for not making all the complementary worksheets. In addition, the number of played levels will be included as a moderator in the analyses.

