### Sample size {14}

Using GLIMMPSE 3.0 [63], the required sample size to conduct multivariate linear mixed models for the primary outcomes quality of life and sibling adjustment to the disability of the brother or sister is calculated. The sample size is estimated with an alpha of 0.05 and a target power of 0.80 and is based on an interaction effect hypothesis, including between (intervention) and within (measurement point) variance. Correlations between measurement points are estimated to be 0.60 (T0–T1; T1–T2) and 0.40 (T0–T2), based on previously found test-retest correlations on the PedsQL [64]. The correlation between the outcomes is estimated to be 0.30. This estimate is based on a previously found correlation between the SPQ and a measure of wellbeing and adjustment (Strengths and Difficulties Questionnaire; SDQ), as no information about the correlation between de SPQ and a measure of quality of life was available [65]. A scale factor of 1.2 for variability is inserted in the sample size calculation, in order to be more conservative.

For both quality of life and sibling adjustment to the disability of the brother or sister the child-report means and standard deviations from previous sibling studies are used [41, 66]. For the control group, no change is expected on the outcome measures. For the intervention group, change is expected gradually. The expected total change (at T2) on quality of life is based on the Minimal Clinically Important Difference [67]. The expected total change on sibling adjustment to the disability of the brother or sister is based on the measured change in a previous sibling intervention study [41]. No change in standard deviations is expected on all measurement points.

The computed sample size calculation based on the beforementioned parameters results in a required sample size of 134, with 67 participants in the intervention group and 67 participants in the waitlist control group. Based on two previous intervention studies [22, 29], a dropout rate of 15% is accounted for. The total required sample size is therefore 154. This includes 154 siblings and their 154 parents.

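### Both planned robustness analyses leave out every study dropout, so neither shows how the result depends on the missing-at-random assumption behind maximum likelihood

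*Protocol article*

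**What the plan says.** All of this stands in the protocol article's section on non-adherence and missing data, item {20c}, unless another place is named.

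- Population of the main analysis: "All participants that are randomized, including treatment dropouts and study dropouts will be included in the main analysis".
- Missing scores: "Maximum likelihood estimation will be used for missing data". The assumption behind this is not named; in a likelihood-based mixed model it is missing at random.
- Robustness: "In order to determine the robustness of the results, two sensitivity analyses will be conducted". The first is "one with the data of all participants that completed all assessments and the intervention". The second is "one with the data of all participants that completed all the assessments but not the intervention (treatment dropouts").
- Definition: "Participants will be considered a treatment dropout when they did not complete the game". This is about adherence, not about missing outcome scores.
- A further adherence analysis: "In addition, the number of played levels will be included as a moderator in the analyses".
- Sample size {14}: "a dropout rate of 15% is accounted for", which takes 134 to 154.
- Plans to promote retention {18b}: no further outcome data are gathered from families who no longer want to be assessed.

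**The concern.** Under maximum likelihood, a game-arm child who leaves is in effect given the game-arm course expected from that child's earlier scores. Whether that is fair cannot be seen in the data, because nothing is observed after the child leaves. A robustness analysis for this problem has to keep the leavers and change what is assumed about them. The two planned analyses remove the leavers and vary only whether the game was finished.

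The trial is open after the pre-test. Waitlist children can play only after the follow-up visit, which gives them a reason to stay that game-arm children do not have. Reasons for leaving may therefore differ by arm. The trial could then report that its result held up in sensitivity analyses when neither of them examined loss to follow-up.

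**Working it through.** **1. The plan's own figure.** Inputs from Sample size {14}: 134 required, 15% dropout, total 154. 134 × 1.15 = 154.1, which reproduces 154. (Dividing gives 134 / 0.85 = 157.6; nothing below depends on the difference.) The 134 itself cannot be rebuilt, because the means, standard deviations and expected changes are not printed. It is not needed here.

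**2. Who enters each analysis.** At 15%, 154 × 0.15 = 23.1 children leave and 154 × 0.85 = 130.9 have complete assessments.

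| Analysis | Study dropouts included | What it varies |
|---|---|---|
| Main, all randomised, maximum likelihood | yes, about 23 | – |
| Sensitivity 1: complete assessments, game finished | none | adherence |
| Sensitivity 2: complete assessments, game not finished | none | adherence |
| Levels played as moderator | not a change in the missing-data assumption | adherence |
| Sensitivity analysis under additional analyses {20b} | not a change in the missing-data assumption | adjustment for baseline differences |

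No row changes what is assumed about the unseen scores.

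**3. Size if the lost children gained nothing.** Assumptions, not in the document: a share p of the game arm is lost before T1, those children have no benefit, and their earlier scores do not reveal this. Maximum likelihood then targets the continuers' effect d, while the effect over all randomised children is (1 − p)d. The ratio is 1 / (1 − p):

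- p = 0.10: 1 / 0.90 = 1.11
- p = 0.15: 1 / 0.85 = 1.18
- p = 0.20: 1 / 0.80 = 1.25

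If d = 0, this mechanism gives no bias.

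**4. Size under a delta shift.** Assume that game-arm leavers are worse at T2 than maximum likelihood predicts by δ standard deviations. The bias is p × δ. At p = 0.15:

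- δ = 0.25: 0.15 × 0.25 = 0.04 SD
- δ = 0.5: 0.15 × 0.5 = 0.075 SD
- δ = 1.0: 0.15 × 1.0 = 0.15 SD

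With the same shift in both arms the bias is (p game − p waitlist) × δ, which is zero when dropout is equal.

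**5. Can comparison with completers reveal the problem?** Simulation with 77 per arm, true effect zero and the plan's correlations (0.60 for adjacent visits, 0.40 for T0–T2). Loss occurs after T0, about 14% in the game arm with lower scores more likely to leave, and 15% at random in the waitlist arm. Bias in the T2 difference between arms:

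| Game-arm loss depends on | Maximum likelihood | Completers |
|---|---|---|
| observed T0 score | 0.00 SD | 0.05 SD |
| unobserved T2 score | 0.10 SD | 0.12 SD |

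The plan tests intervention by time, so the change from T0 also matters. Maximum likelihood keeps every T0 score, so its bias is unchanged. For completers the T0 scores shift too:

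- Loss on T0: the T0 shift is 0.05 / 0.40 = 0.125, so the bias in change is 0.05 − 0.125 = −0.075 SD.
- Loss on T2: the T0 shift is 0.40 × 0.12 = 0.048, so the bias in change is 0.12 − 0.048 = 0.072 SD.

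On change, the two methods differ by about 0.08 SD when maximum likelihood is unbiased, and by about 0.03 SD when it is biased by 0.10 SD. Agreement with a completers analysis is therefore no evidence that the assumption holds.

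**The case against.** **This may be only an omission.** The article condenses a fuller protocol, and a statistical analysis plan may add an analysis that departs from missing at random. That would count if {20c} were silent. It is not silent: it sets two analyses, states their purpose, and both condition on complete data. The point rests on that text.

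**The two analyses are adherence analyses and are never called missing-data checks.** This is right. A reader might infer that the plan presents them as tests of the missing-data method, and the text does not say so. But they are offered for the robustness of the results in a section that covers both non-adherence and missing data, and nothing else there serves the second purpose. Clear labelling would settle this.

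**No analysis can test missing at random.** This also stands. It is tempting to say that the plan fails to test the assumption, but observed data cannot do that. A sensitivity analysis can only show how far the conclusion moves under other assumptions.

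**Stopping the game is not leaving the study.** A reader might infer that children who tire of the game will usually leave the assessments too. The documents do not support that. The discontinuation section {11b} has families who stop playing asked whether they will still complete assessments, and {18b} adds continued contact, a pre-booked visit and a reminder. Children who stop playing but stay contribute observed scores. Their results and the levels-played moderator also give some indirect, imperfect evidence about those who left.

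**The inflation is built in by assumption.** It is. The 15% is an overall planning figure, not a game-arm rate before T1, and zero benefit in every lost child is the unfavourable end. A reader should not infer that the estimate will be 18% too large, or that withdrawal is the main threat to the trial.

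**Conclusion.** The point holds in a limited form. The robustness analyses fixed in {20c} cannot show how the main result depends on what maximum likelihood assumes about study dropouts, because they contain none of them. Restricting to completers does not relax that assumption; it puts a stronger one in its place.

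The size of any bias cannot be known from the document. The factors of 1.11 to 1.25 hold only for 10% to 20% game-arm loss before T1 with no benefit in those lost. The shifts of 0.04 to 0.15 SD hold only for 15% game-arm loss with an assumed departure of 0.25 to 1.0 SD confined to that arm. Later loss makes the bias smaller, and equal dropout with equal departure in both arms makes it zero. The documents do not show that the main analysis is biased. They show that the planned checks would not reveal it if it were. The change is worth making because it costs little.

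**What to change.** In {20c}:

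1. Label the two existing analyses as adherence analyses.
2. Add one sensitivity analysis of all randomised children that departs from missing at random. It should cover the two primary outcomes, child and parent report separately, at T1 and T2. One suitable form is control-based multiple imputation: missing scores of game-arm dropouts are drawn from the waitlist-arm distribution given each child's own earlier scores.
3. Apply a delta shift to the game arm's imputed scores over a range stated in advance, and report where, if anywhere in that range, the intervention-by-time conclusion changes for each outcome and reporter.

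This takes a few sentences in the plan and a few extra analysis runs on data already held. The downside is a possibly less favourable secondary estimate reported beside the main one. The main analysis and the sample size stay as they are.

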### Plans to give access to the full protocol, participant-level data, and statistical code {31c}

The full protocol is available upon reasonable request. The anonymized dataset of only the quantitative data and the statistical code will be accessible for other researchers upon request. Data requests will be reviewed by the researchers and data sharing agreements will need to be signed.

### Composition of the data monitoring committee, its role and reporting structure {21a}

A data monitoring committee (DMC) is not needed, as participation in the study does not have risks for the participants.

### Adverse event reporting and harms {22}

It is not expected that any adverse events will take place during this study. There are no risks. However, when unexpected adverse events take place, these will be reported to the medical-ethical committee (METc VUmcC).

### Frequency and plans for auditing trial conduct {23}

This study is embedded in the research institute Amsterdam Public Health (APH; reference: SQC2022-023). Part of the APH quality control of research projects is to randomly select a study for an audit. The study will be conducted according to APH standards.

### Plans for communicating important protocol amendments to relevant parties (e.g., trial participants, ethical committees) {25}

Important protocol modifications will be reported to and need to be approved by the medical-ethical committee (METc VUmc). When modifications are approved, these will also be reported to the participants, and be added to the Trials paper and the study registration on ClinicalTrials.gov.

### Dissemination plans {31a}

The outcomes of this study about the effectiveness of the intervention will be reported in article(s) in international peer-reviewed journals. Both positive and negative outcomes will be reported. The outcomes will also be reported in professional magazines in the field and in magazines for parents. The results will be presented in participating care organizations and at scientific conferences.

## Discussion

The support for siblings of children with disabilities is scarce and fragmented, even though studies have shown that these siblings can benefit from support [6]. Although several interventions for siblings have been developed, these are costly and time-consuming and the effects have not been studied with randomized controlled trials. This study will investigate the effectiveness of the first serious game for siblings (aged 6–9 years) of children with ID and/or VI, using an RCT design.

The serious game, named “Broodles,” is an educational game that siblings can play without assistance of an adult. The game consists of eight 20-minute levels that all have the same structure of eight game elements. The serious game aims to improve sibling’s quality of life, adjustment to their bother’s or sister’s disability, and multiple aspects of psychosocial wellbeing, through helping them to better understand and deal with thoughts, feelings, and difficult situations.

The expectation is that the current study will contribute to the development of support sources for siblings of children with disabilities. If the outcomes of this study show that the serious game is effective, the game will be readily available to all siblings through an open webpage. This gives parents, teachers, and caregivers tools to support siblings. Because one can never know the impact of the care burden on the family, due to different social and additional circumstances, and a care system that has only been focused on the child with a disability, it is first of all important for the game to be free of charge and that siblings are able to play it without assistance. And yet, as siblings belong to the family context and all members have an effect on each other’s wellbeing, the serious game could, when proven to be effective, preferably be offered by care organizations as part of a family intervention. This can be supportive because, based on clinical practice (in the Netherlands and Belgium), it has become clear that there is a lack of structural acknowledgment of siblings’ needs and that siblings are often forgotten when offering family interventions. The serious game may raise more awareness of the role, and thoughts and feelings of siblings. It can also be a referral to other and more intensive support sources for siblings who need extra help. Also, the close collaboration with care organizations can contribute to the implementation of the serious game in practice.

Additionally, this study will contribute to the knowledge about siblings’ support needs and sibling interventions. Few randomized controlled trials have been executed in the field of serious games for children and the field of sibling interventions [16–18, 20]. Besides, the qualitative measures may provide more insight into which aspects of the intervention siblings and parents experience as helpful. This could give direction to future research about this or other interventions for siblings. Finally, this study will be the first to specifically examine an intervention focusing on contributing to the well-being of siblings of children with VI.

Previous research shows that it remains unclear whether a sibling intervention should be offered to siblings of children with a specific diagnose type or not [16]. In order to develop a game that addresses situations that siblings can relate to the most, we did select a specific group for this study. However, when the game is found to be effective for this population, it can be investigated if the game is also effective for a broader group of siblings.

In conclusion, siblings of children with disabilities should also be supported, although there are only a few evidence-based interventions. The present study will provide insight into the effectiveness of the newly developed serious game “Broodles” in improving quality of life, adjustment to the disability of the brother or sister, and multiple aspects of psychosocial well-being of siblings of children with ID and/or VI. If this first serious game is proven to be effective, it can be used as a free of charge, easily accessible, preventive intervention for siblings.

## Trial status

Recruitment started on March 22, 2022, in the Netherlands and Belgium, and the first participant was enrolled on April 22, 2022. The first assessment started on April 22, 2022. Recruitment will continue until the required sample size is met, or at a maximum up until December 2023.

Protocol version 1, May 2022

## Data Availability

The pseudonymized dataset of the quantitative data will be made available upon reasonable request at DataverseNL.

## Abbreviations

APH: Amsterdam Public Health
CPRS: Child-Parent Relationship Scale
CSI: Coping Strategies Inventory
GLIMMPSE: General Linear Multivariate Model Power and Sample Size
ID: Intellectual disability
METc: Medical Ethics Committee
PAIR: Pictorial Assessment of Interpersonal Relationships
PedsQL: Pediatric Quality of Life Inventory
PEPC-SRQ: Parental Expectations and Perceptions of Children’s Sibling Relationships Questionnaire
PSOC: Parenting Sense of Competence Scale
RCT: Randomized controlled trial
SPPC: Self-Perception Profile for Children
SPSS: Statistical Package for the Social Sciences
SPQ: Sibling Perception Questionnaire
SSSC: Social Support Scale for Children
SVS: Social Validity Scale
VI: Visual impairment
VUmc: Vrije Universiteit Medical Center
WHO: World Health Organization
